## Abstract

**Introduction:**

Transverse myelitis (TM) is an immune-mediated disorder of the spinal cord which causes motor and sensory disturbance and limited recovery in 50% of patients. Standard treatment is steroids, and patients with more severe disease appear to respond to plasma exchange (PLEX). Intravenous immunoglobulin (IVIG) has also been used as an adjunct to steroids, but evidence is lacking. We propose the first randomised control trial in adults and children, to determine the benefit of additional treatment with IVIG.

**Methods and analysis:**

170 adults and children aged over 1 year with acute first episode TM or neuromyelitis optica (with myelitis) will be recruited over a 2.5-year period and followed up for 12 months. Participants randomised to the control arm will receive standard therapy of intravenous methylprednisolone (IVMP). The intervention arm will receive the above standard therapy, plus additional IVIG.

Primary outcome will be a 2-point improvement on the American Spinal Injury Association (ASIA) Impairment scale at 6 months postrandomisation by blinded assessors. Additional secondary and tertiary outcome measures will be collected: ASIA motor and sensory scales, Kurtzke expanded disability status scale, International Spinal Cord Injury (SCI) Bladder/Bowel Data Set, Client Services Receipt Index, Pediatric Quality of Life Inventory, EQ-5D, SCI Pain and SCI Quality of Life Data Sets. Biological samples will be biobanked for future studies. After 6-months' follow-up of the first 52 recruited patients futility analysis will be carried out. Health economics analysis will be performed to calculate cost-effectiveness. After 6 months’ recruitment futility analysis will be performed.

**Ethics and dissemination:**

Research Ethics Committee Approval was obtained: 14/SC/1329. Current protocol: v3.0 (15/01/2015). Study findings will be published in peer-reviewed journals.

**Trial registration numbers:**

This study is registered with EudraCT (REF: 2014-002335-34), Clinicaltrials.gov (REF: NCT02398994) and ISRCTN (REF: 12127581).

Strengths and limitations of this studyThe first randomised multicentre UK trial in children and adults with transverse myelitis or neuromyelitis optica, recruiting 170 patients over 2.5 years with a 12-month follow-up period.Outcome measures will include motor, sensory, functional and quality of life measurements by blinded assessors.Health economics analysis will include health and social care costs.Findings may inform treatment decisions in other rare, inflammatory central nervous system disorders.High recruitment rate required due to low incidence of condition.

## Introduction

Transverse myelitis (TM) is a rare inflammatory disorder of the spinal cord affecting approximately 350 children and adults annually in the UK.^1^
^2^ Histologically, TM is characterised by spinal cord immune cellular infiltration, and pathogenesis is mediated by a variety of immunological mechanisms.^3^ Clinical features include a rapid onset of motor, sensory and autonomic dysfunction, and a prolonged recovery phase which may continue for up to 4 years.^4^ Diagnostic criteria for TM were established by the TM Consortium Working Group in 2002, to distinguish TM from other conditions including MS and a clinically isolated syndrome.^5^ A proportion of patients initially diagnosed with TM will subsequently relapse, often with involvement of other parts of the central nervous system, and may often be diagnosed with either multiple sclerosis (MS) or neuromyelitis optica (NMO). However, a proportion of patients remain as relapsing TM of as yet unknown aetiologies.

NMO is a relapsing subset of TM, caused by antibodies to aquaporin-4, an astrocytic water channel.^6^ Clinically, patients have predominantly recurrent episodes of myelitis and optic neuritis. Initial presentation may be with myelitis alone, making it clinically and radiologically indistinguishable from TM, and patients are thus subjected to the same acute therapeutic strategies.

The American Spinal Injury Association (ASIA) international standards for neurological classification of spinal cord injury enables a standardised assessment of neurological outcome, where A is no sensory or motor function in S4–5, and E is normal function.^7^ Retrospective data from paediatric cohorts suggest that 30% have ASIA A-C or expanded disability status scale (EDSS) ≥4 after TM,^8^ and a retrospective French multicentre study in adults found that 36% had a poor prognosis as defined by death or non-ambulatory status with current therapy.^9^ Since this is primarily a disease of younger people, this results in significant cumulative demands on health and social care resources.

There are no robust controlled trials in children or adults to inform on the optimal treatment of TM. Standard treatment with intravenous methylprednisolone (IVMP) is based on class IV evidence that it shortens relapse duration and speeds recovery in exacerbations of adult multiple sclerosis.^6^
^10–12^ Given the disease severity and poor outcomes, plasma exchange (PLEX) has been used in addition to standard therapy. Addition of PLEX showed benefit in two studies: a retrospective analysis of 122 adults with TM;^10^ and a small randomised controlled trial (RCT) in adults with a steroid unresponsive acute central nervous system (CNS) demyelination which included four patients with TM.^13^ However, PLEX is not universally available in the NHS, particularly at short notice and on weekends, and can be technically difficult and costly to administer.^14^

Randomised controlled trials have demonstrated IVIG efficacy in a number of neurological conditions.^15^ In steroid-unresponsive CNS demyelination, IVIG is often used, although supporting data are limited to small case series and single case reports.^16^
^17^ IVIG appears to inhibit complement binding, neutralise pathogenic cytokines, downregulate antibody production, enhance remyelination and modulate phagocytosis and T-cell function.^18^ The majority of these factors are common across inflammatory disorders of the CNS including TM,^19^ providing a strong rationale for its use. The availability, ease of administration, familiarity and safety also make IVIG an attractive option in the acute setting.

### Trial objectives and design

This multicentre, single blind, parallel group RCT will generate evidence to inform clinical and health economic decisions regarding IVIG use in adults and children with TM.

### Primary objective

To evaluate if additional and early treatment with IVIG is of extra benefit in TM when compared to the current standard therapy of IVMP.

### Secondary objectives

The clinical and paraclinical data collected from patients will provide a robust resource and platform for other clinical studies, including identification of early predictors of poor outcome.Biobanked samples from patients recruited to the study will be collected and used for carefully designed biological studies by a consortium of established basic science researchers in the field.

## Methods

### Study setting

Treatment and follow-up will be in the participating tertiary neurology centres, and recruitment will also occur from feeder district general hospitals and rapid general practitioner (GP) referrals. For further details on participating centres and trial registration, please see online supplementary appendix 1.

### Eligibility criteria

#### Inclusion criteria

Patients must satisfy all inclusion criteria to be eligible for recruitment. They will be eligible if all of the following apply at the time of randomisation:
Age 1 year or overDiagnosis of EITHER acute first onset transverse myelitis (using the TM Consortium Working Group 2002 criteria^6^)—patients must fulfil all of the following criteria:
Sensory, motor or autonomic dysfunction attributable to spinal cord diseaseBilateral signs and/or symptoms (not necessarily symmetric)Sensory level (except in young children <5 years where this is difficult to evaluate)Lack of MRI brain criteria consistent with multiple sclerosis^20^Progression to nadir between 4 h and 21 daysOR first presentation of neuromyelitis optica (using standardised criteria^21^)—patients must fulfil both absolute criteria:
Optic neuritisAcute myelitisplus two out of three supportive criteria (as AQP4 is often not available acutely, only the first two supportive criteria would be applied):
Brain MRI not meeting criteria for MS at disease onsetSpinal cord MRI with contiguous T2-weighted signal abnormality extending over three or more vertebral segments, indicating a relatively large lesion in the spinal cordAquaporin 4 IgG seropositive statusASIA Impairment Score of A-CRandomisation to occur no later than day 5 of steroids, and, if definitely known, within 21 days from symptom onset.Give assent (8–16 years)/consent to participate in the trial.

#### Exclusion criteria

In addition to failing to meet the inclusion criteria, exclusion criteria include any of the following:
Contraindication to IVIG as stated in the product SmPC, or receiving IVIG for other reasonsPreviously known systemic autoimmune disease (eg, systemic lupus erythematosus) or any evidence of systemic inflammation during current presentation.Direct infectious aetiology (eg, varicella zoster)Previous episode of CNS inflammatory demyelinationAcute disseminated encephalomyelitis (ADEM)Other causes of myelopathy not thought to be due to myelitis (eg, nutritional, ischaemic, tumour, etc)Other disease which would interfere with assessment of outcome measuresKnown pregnancyCircumstances which would prevent follow-up for 12 months.

### Interventions

Patients randomised to the **control arm** of this study will be prescribed IVMP. Paediatric patients will receive 30 mg/kg or 500 mg/m^2^ capped to a maximum dose of 1 g/day for 5 days. Adult patients will be given 1 g/day for 5 days. Clinicians may follow this with an oral steroid taper according to local practice.

Patients randomised to the **intervention arm** will receive the above standard therapy *plus* additional IVIG at a total dose of 2 g/kg. Doses will be divided over 2 days (children <41.2 kg) or 5 days (all other patients) and individual doses may vary slightly to minimise drug wastage and anticipate for difficult intravenous access in small children.

Treatment failure will be defined as no improvement 14 days after presentation and/or 5 days after completion of treatment, and will be documented. Rescue therapy may be initiated at this point. Given the therapeutic effect of PLEX, treatment will be standardised to comprise five cycles in which at least 75% of plasma volume is exchanged, with a gap of 24–48 h between cycles. An additional course of IVMP may be given if there is a delay between the decision to start PLEX and therapy initiation, at the discretion of the treating clinician. The duration and intensity of neurorehabilitation input will be recorded to enable comparison between groups.

### Outcome measures

Outcome measures have been selected to give a ‘hard’ clinical end point that will have clinical significance, and will be assessed at the local centre by a blinded assessor. To minimise loss to follow-up, assessments are timed to coincide with routine clinical follow-up. All outcome measures are internationally accepted scales, and the primary outcome measure is the ASIA Impairment scale, which is used to measure disability in TM.^22^ A 6-month time point has been selected, as the majority of neurological recovery is likely to have occurred by this point. Additional data points will be taken at 3 and 12 months to aid statistical analysis.

#### Primary outcome measure

A two point or greater improvement in the ASIA scale (classified A-E) at 6 months postrandomisation, when compared to baseline, will indicate a positive outcome.

#### Secondary outcome measures

A change in the ASIA motor scale (0–100) and sensory scale (0–112)A change in the Kurtzke expanded disability status scale (EDSS) with Neurostatus scoringEQ-5D-Y (patients aged 8–12 years at presentation) or EQ-5D-5 L (patients aged ≥13 years at presentation)International SCI Quality of Life Basic Data Set (patients aged ≥13 years)Client Service Receipt Inventory (CSRI).

#### Tertiary outcome measures

International SCI Bladder/Bowel Data Set (patients aged ≥13 years)International SCI Pain Basic Data Set (patients aged ≥13 years)Pediatric Quality of Life Inventory TM (PedsQL Parent Report for Toddlers; patients aged 2–4 years)Pediatric Quality of Life Inventory TM (PedsQL Parent Report for Young Children; patients aged 5–7 years).

### Participant timeline

Patients will be enrolled to the study for 1 year (table 1).

**Table 1 BMJOPEN2015008312TB1:** Timeline of trial interventions

Schedule Treatment day (TD) Time point (T)	T0 (Screening, baseline and prediagnosis tests)	T1 (Treatment and discharge)							T2 3M	T3 6M	T4 12M	Withdrawal
		TD 1*	TD 2	TD 3	TD 4	TD 5	Rescue therapy†	Discharge				
Screening with diagnostic algorithm and core investigations including physical examination	X											
Patient information and informed consent	X											
Eligibility form	X											
Registration form	X											
Prediagnosis tests—for example, MRI and AQP4	X											
Randomisation	X											
Biobank samples	X									X		
ASIA Impairment Score (A-E)	X						X	X	X	P	X	
ASIA Motor and Sensory Score	X						X	X	X	S	X	
Neurostatus scoring (Kurtzke functional systems and EDSS)	X							X	X	S	X	
8–12 years EQ-5D-Y	X								X	S	X	
≥13 years EQ-5D-5L	X								X	S	X	
≥13 years SCI QoL Basic data set									X	S	X	
CSRI									X	S	X	
≥13 years SCI Bladder										T	X	
≥13 years SCI Bowel										T	X	
5–7 years Peds QL										T	X	
2–4 years Peds QL										T	X	
Treatment form						X						
Concomitant medications								X	X	X	X	
Discharge form								X				
Rescue therapy form (if needed)†							X					
Relapse form (at any time point if needed)†								X	X	X	X	
Adverse events‡		X	X	X	X	X						
Study Status Form									X	X	X	
Withdrawal form (at any time point)†												X

*Treatment day 1: IVIG treatment (if applicable) to start on the same day as randomisation. Steroids may be started up to 5 days prior to randomisation.

†Rescue therapy, relapse and withdrawal forms may only be necessary for a small subset of patients.

‡Adverse events will be collected throughout the study.

ASIA, American Spinal Injury Association; AQP4, aquaporin-4; CSRI, Client Service Receipt Inventory; EDSS, expanded disability status scale; Peds QL, Pediatric Quality of Life Inventory; P, primary outcome measure; S, secondary outcome measure; SCI, Spinal Cord Injury; T, tertiary outcome measure.

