### Sample size

The power analysis has taken into account the inclusion of a futility analysis to be undertaken after recruitment of one-third of the target sample. We have assumed that the proportion of participants showing a two-point improvement (or greater) on the ASIA Impairment scale will be approximately 0.5 (50%) in the control arm and a minimum of 0.75 (75%) in the intervention arm, based on available data from epidemiological studies.^2^
^7^ The sample size calculation is based on the conservative assumption of no correlation between repeated measures. Under these assumptions, 76 patients per group will provide 90% power and 5% type II errors for a two-sided test. The sample size will be inflated for attrition; on the basis of our experience and the design which minimises loss to follow-up, we estimate 10% attrition. This requires a recruitment of 170 patients (85 participants per arm).

The ASIA total motor score (0–100) is a secondary outcome. Stata ‘*sampsi*’ indicates that using an Analysis of Covariance with a baseline to end point correlation of 0.6, there will be 87% power to detect a difference between the control and treatment arms of a medium to large effect size of 0.4. Such a difference will be of clinical significance.

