### Randomisation

Prior to randomisation but after consent, site staff will register a recruit on the web-based electronic data capture system (InferMed MACRO), hosted at the King's Clinical Trials Unit (KCTU). Each will be assigned a unique study patient identification number (PIN) by the system. Once baseline assessments are complete, the trained trial staff will access the KCTU randomisation system and randomise the patient at the individual level using stratified block randomisation by service type (adult or child); the block will randomly vary in size. Treatment allocation will be at a ratio of 1:1. Randomisation will occur during office hours when IVIG is available. Patients eligible for trial recruitment presenting outside of these times will be started immediately on IVMP and then randomised at the first available opportunity.

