### Statistical methods

#### Primary analysis

If the study continues to full recruitment, analyses of effectiveness will be pragmatic, based on the intention-to-treat (ITT) sample. The significance level will be 5% (two-sided) for specified analyses. The estimated effect size and its precision (95% CIs) will be presented for all outcomes. The main statistical analyses will establish the effectiveness of IVIG against standard therapy at 6 months postrandomisation (see primary end points above). To this end, linear mixed modelling (LMM) will be employed. In such models, the binary outcome variable measured at the post-treatment time points (3, 6 or 12 months) features as the dependent variable with outcome at baseline (if applicable), stratification factors (service level), treatment arm and a treatment x time interaction term included as covariates. To account for correlation between repeated measures on the same individual, a subject-varying random intercept will be included. Mixed effects logistic regression can be completed using the ‘*xtmelogit’* command in Stata.

There are expected to be some missing data in the post-treatment outcome variables. The LMM analyses are based on maximum likelihood and will provide valid inferences under a missing at random (MAR) missingness mechanism.

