#### Secondary analyses

The secondary clinical assessments (EDSS, ASIA motor and sensory scales, SCI data sets, PedsQL, EQ5D and CSRI) with repeated measurements will also be analysed within a LMM framework where generalisations of the LMM will be utilised to allow for outcomes with non-normal data if necessary. Those measures with one follow-up assessment will be evaluated with in a Generalised Linear Model. The dependent variable will feature as the outcome measure. The covariates will be the corresponding baseline measure (if applicable), stratification factors and treatment group.

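### Outcomes with no baseline value in Table 1 are adjusted for service type only, although a baseline ASIA motor score is scheduled for everyone: an optional gain in precision of uncertain size

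*Protocol article*

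**What the plan says.** **Schedule.** In the Protocol article, Table 1 (Participant timeline), the T0 cell is blank for:

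- "≥13 years SCI QoL Basic data set" and CSRI, both first taken at 3 months;
- "≥13 years SCI Bladder", the matching bowel row, "5–7 years Peds QL" and the PedsQL row for ages 2 to 4, all first taken at 6 months.

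The same table marks T0 for "ASIA Motor and Sensory Score" and for EDSS, neither with an age limit. It also marks T0 for EQ-5D, but only from age 8 (EQ-5D-Y at 8 to 12 years, EQ-5D-5L from 13).

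**Covariates.** The Primary analysis section gives the mixed-model terms: "outcome at baseline (if applicable), stratification factors (service level), treatment arm and a treatment x time interaction term included as covariates". The Secondary analyses section puts outcomes with repeated measurements in that framework and, after turning to measures with a single follow-up, adds: "The covariates will be the corresponding baseline measure (if applicable), stratification factors and treatment group". The Randomisation section names one stratification factor, service type (adult or child).

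**Planned use of a baseline elsewhere.** For the ASIA motor score, the Sample size section claims 87% power from an analysis of covariance with "a baseline to end point correlation of 0.6" and an effect size of 0.4.

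**The concern.** Where an outcome has no T0 value, the baseline term drops out of the model and the plan names nothing in its place. This leaves two of the five listed secondary outcomes (SCI QoL and CSRI), and the bladder, bowel and PedsQL tertiary outcomes, with no adjustment for severity at entry. Patients enter with ASIA grades A to C, so severity does vary. A secondary objective is to identify early predictors of poor outcome, so the investigators themselves expect entry data to be prognostic.

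At stake are confidence intervals wider than the collected data would allow. SCI QoL, bladder and bowel apply only from age 13 and PedsQL only at 2 to 7 years, so these analyses already start with fewer patients.

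**Working it through.** **1. Which rule governs.** Each listed outcome has two or three follow-ups in Table 1, so it falls under the mixed model rather than the single-follow-up model. The covariate sentence in Secondary analyses is therefore not clearly the governing one. The Primary analysis section states the same rule for the mixed model, so both routes lead to service type as the only baseline covariate.

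**2. Reproducing the plan's figure.** Inputs from Sample size and Primary analysis: n = 76 per arm, d = 0.4 SD, r = 0.6, two-sided 5%. For one time point:

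power = Φ( d / √[(1 − r²) · 2/n] − 1.96 )

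- √(2/76) = 0.1622, and 0.4/0.1622 = 2.466.
- With r = 0.6, √(1 − 0.36) = 0.8, so 2.466/0.8 = 3.082 and Φ(1.122) = 0.869. This agrees with the stated 87%.
- With no baseline covariate, Φ(2.466 − 1.96) = 0.694.

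**3. Applying it to outcomes without their own baseline.** Here r is the correlation, within service type, between T0 motor score and the later outcome. The article does not give it, so it is varied. The 0.4 SD effect is the plan's figure for motor score and only illustrates these outcomes.

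| Assumed r | Cut in residual variance, r² | Effective sample size, 1/(1 − r²) | Power at 76 per arm |
|---|---|---|---|
| 0 (service type only) | 0% | 1.00 | 69.4% |
| 0.1 | 1% | 1.01 | 69.8% |
| 0.2 | 4% | 1.04 | 71.1% |
| 0.3 | 9% | 1.10 | 73.4% |
| 0.4 | 16% | 1.19 | 76.7% |
| 0.5 | 25% | 1.33 | 81.3% |
| 0.6 (ceiling) | 36% | 1.56 | 86.9% |

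The last row is a ceiling because 0.6 is the plan's correlation of motor score with itself over time. A different outcome would not be expected to track T0 motor score more closely than that.

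**4. Age subsets.** The article gives no numbers by age. With an assumed 50 per arm aged 13 or over, the same formula gives 51.6% with no covariate, 55.4% at r = 0.3 and 63.7% at r = 0.5. With an assumed 20 per arm it gives 24.4% and, at r = 0.3, 26.3%.

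**5. Which T0 measure can serve.** Motor score can serve all the listed outcomes. EQ-5D cannot: PedsQL covers ages 2 to 7, where no EQ-5D is taken, and CSRI carries no age limit, so its patients under 8 would have no value. For SCI QoL (age 13 and over), T0 EQ-5D-5L is scheduled.

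**The case against.** The strongest reply is that nothing here is wrong. Both covariate lists make the baseline term conditional, so outcomes without a baseline were foreseen, and adjusting for the stratification factor alone gives a valid randomised comparison. That stands: there is no contradiction and no bias.

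Second, the choice of further covariates often belongs in the analysis plan, and the article refers to the full protocol and an appendix for more detail. A substitute may already be named there. This also stands as a caution, but the article states a rule, and the point is that the rule can be improved.

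Third, the size is not known. No correlation with these outcomes is given, entry limited to ASIA A to C may narrow the spread of motor scores and weaken it, and at r = 0.1 the gain is only 0.4 points of power. The formula assumes a continuous outcome with constant variance, which may not suit CSRI (the economic analysis plans bootstrapping for skewed results) or the bladder and bowel data. Nor do the documents show that motor score is a better choice than EDSS. All of this limits the claim without removing it, because the cost is so small.

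Two stronger readings are tempting. A reader might infer that chance imbalance in severity biases these comparisons. It does not: under randomisation, the unadjusted interval and the 5% error rate already allow for it. A reader might also take the gap between 86.9% and 69.4%, 17.5 points, as the power these outcomes lose. The documents do not support that, since it borrows motor score's correlation with itself, and the article claims no power for any of these outcomes.

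**Conclusion.** The point holds as an efficiency improvement in secondary and tertiary outcomes. As written, SCI QoL, CSRI, SCI bladder, SCI bowel and PedsQL are adjusted for service type only, and a T0 severity measure scheduled for every patient is left out. The primary outcome, its sample size and the futility rule are untouched.

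The gain cannot be fixed from the article. For a continuous outcome analysed at one time point, an assumed r between 0.1 and 0.5 gives a gain of 0.4 to 11.9 points of power at 76 per arm and 0.4 SD (69.8 − 69.4 and 81.3 − 69.4). For r of 0.2 to 0.4 it is about 2 to 7 points. Priority: optional.

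**What to change.** Add to Secondary analyses, or confirm that the analysis plan already says so:

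> For outcomes with no T0 measurement in Table 1, the model will include baseline ASIA motor score as a covariate (and baseline EQ-5D-5L for SCI QoL, ages 13 and over); baseline EQ-5D will not be used for PedsQL or CSRI.

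The cost is one sentence and one or two degrees of freedom per model, with no new data collection. The lost degrees of freedom matter most in the small PedsQL age groups. The sentence should be settled before any unblinded outcome data are seen, because a covariate chosen afterwards would be open to challenge.
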